## 9.3. Case Definitions

Outcomes will be based on the following case-definitions:

### 9.3.1. Undiagnosed infectious (prevalent) TB

**Definite:** A participant investigated because of symptoms or an abnormal chest radiograph identified during the pre-intervention survey, **and at least 2 sputum samples testing positive** for TB (microscopy, Xpert or culture). Sputum specimens taken during follow-up can contribute to meeting this case-definition provided that at least one prevalence survey specimen was positive.

**Probable:** A participant investigated because of symptoms or an abnormal chest radiograph identified during the pre-intervention survey, **and 1 sputum sample testing positive** for TB (microscopy, Xpert or culture), **and either** a compatible clinical illness with decision to treat for TB on clinician's review **or** loss to clinical follow-up due to illness or death. Sputum specimens taken during follow-up can contribute to meeting this case-definition if the chest radiography is considered on review to be consistent with TB.

**Uncertain TB status:** A participant investigated because of symptoms or an abnormal chest radiograph identified during the pre-intervention survey, **and 1 sputum sample testing positive** for TB (microscopy, Xpert or culture) **and either** no evidence of compatible clinical illness on review **or** loss to clinical follow-up due to reasons other than illness or death.

**TB excluded:** A participant with **either** no indications for sputum testing, **or** investigated because of symptoms/abnormal chest radiograph but with decision not to treat for TB due to no evidence of compatible clinical illness on review and complete follow-up.

### 9.3.2. Other epidemiological definitions for prevalent TB

**Undiagnosed:** patients meeting the above case-definitions who are not already on treatment

**Smear-positive:** at least one sputum microscopy result, agreed on by 2 independent readers as being positive in a participant who meets one of the above case-definitions for prevalent TB

### 9.3.3. Routinely diagnosed TB patients

TB patients registering through the routine system do not have a standardised set of investigations for diagnosis. Although most patients have a single sputum specimen taken for the purposes of bacteriological confirmation at the time of treatment, results may be compromised by poor sputum quality, and by the known limitations of sensitivity of a single specimen.

For the purposes of the trial, registering patients will be considered **sputum-positive** if they have at least one positive sputum microscopy or Xpert test recorded, regardless of source (routine, or research laboratory), and **sputum-negative culture-positive** if *M. tuberculosis* is grown from their TB registration specimen with no other positive sputum results recorded.

Patients will be considered to have “**microbiologically-confirmed TB**” if they meet definitions for either **sputum-positive** or **sputum-negative culture-positive TB**.

## **10. INTERVENTIONS, METHODS AND PROCEDURES**

Sensitization and mobilization will be conducted before commencement of study implementation. Blantyre District Health Office and Blantyre District Assembly stakeholders will be briefed on the study to ensure support from these key stakeholders.

Thereafter, sensitization meetings will be carried out in the catchment area of the study. This community sensitization process will be coordinated by HSAs with support from SCALE staff members. The community sensitization meetings will be aimed at:

- Identifying 6 to 10 suitable volunteers that will be supporting study activities in each intervention cluster.
- Underscoring benefits to self, family, and friends of early diagnosis of infectious TB and HIV thereby encouraging participation in the study.

### **10.1. Recruitment**

All recruitment will be population-based, as described below, except for interview of facility attendees being investigated for TB for the qualitative and economic substudies.

### **10.2. Screening and Eligibility Assessment**

Potential participants in the different stages of the study will be screened for eligibility according to the above criteria. Screening and recruitment logs will be kept of all potentially eligible participants, with reasons for non-participation if relevant.

### **10.3. Informed Consent**

Written informed consent will be taken from eligible participants before any trial-specific procedures are undertaken, with witnessed thumbprint used for patients unable to read and/or write. A copy of the signed informed consent will be given to the participant, with one signed copy retained for study documentation. All patient information sheets and consent forms will be translated in to local languages. It will be clearly stated that the participant is free to withdraw from the trial at any time for any reason without prejudice to future care, and with no obligation to give the reason for withdrawal.

### **10.4. Procedures**

#### **10.4.1. Pre-intervention survey participants**

Adult ( $\geq 18$  years) residents from both intervention and non-intervention clusters will be selected using random sampling from all households within the cluster boundaries, aiming for 215 participants per cluster (15,500 in total).

Following written (or witnessed if illiterate) informed consent (Appendix 1.11a&b flyer, Appendix 1.12a&b information sheet and Appendix 1.1a&b consent form), all adults in selected households will be asked to complete a standardised questionnaire including demographics, socioeconomic status, and TB symptoms (Appendix 1.5a&b household questionnaire and Appendix 1.6a&b individual questionnaire).

Mid-upper arm circumference will be measured, and household-level variables including number of adult and child members, approximate dimensions of rooms used for living and sleeping, and cooking arrangements will be recorded.

Particulate matter in the air and the concentration of carbon monoxide will be measured inside study participant's households and in the open area, using hand-held particulate matter and carbon monoxide monitors.

A random selection of participants will be asked to complete an extended questionnaire (see Appendix 1.6a&b individual questionnaire), including questions to ascertain TB knowledge, attitudes and perceptions, gender equitable norms, health service utilization and social contacts mixing.

After completing the questionnaire all participants will be given a referral card for TB screening (Appendix 1.13).

TB screening will then be offered using digital chest radiograph read immediately by an experienced radiologist trained in TB prevalence surveys, with their interpretation supported by computer assisted diagnostics (CAD) (Appendix 1.2a&b consent and Appendix 1.10 CRF). HIV testing will be offered using OraQuick HIV 1/2 and parallel finger-prick Alere (Abbott) Determine™ HIV-1/2. Positive HIV test results will be confirmed using Trinity Biotech Uni-Gold™ (Appendix 1.3a&b consent and Appendix 1.7 CRF).

Participants reporting cough, or with chest radiograph abnormality, will have two sputum samples taken for Xpert, fluorescent microscopy and MGIT culture (Appendix 1.4a&b consent and Appendix 1.8 CRF) and will be followed up with Xpert/microscopy results within 2 days, and culture results within 6 weeks (Appendix 1.9 Lab results CRF). Patients with positive TB results will have confirmatory specimens taken, while being assisted to register for TB treatment at the nearest TB Registration Centre (Appendix 1.14 referral card). A study clinic appointment with clinician's review for further management will be offered to all participants with unexplained chest radiograph abnormalities.

All participants with newly diagnosed HIV will be provided with post-test counselling and assisted to register for ART at their nearest primary care clinic (Appendix 1.15 referral card).

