### **3.7. Timelines:**

3 year study from Sept 2018 to Aug 2021, with the ACF Intervention and all surveys delivered during June 2019 to March 2020.

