| Follow up duration           | 
1-3 months per cluster
 
Pre-intervention survey, 10-11 months of ACF intervention: cluster-initiation will be staggered over 9-months
                                                                                                                                                                                                                                                                                                                                                                   |                                                                                                                                                                                                                                                                                                                                                                                                                                                                                                          |
| Planned recruitment period   | June 2019-Mar 2020: pre-intervention survey and ACF Round 1                                                                                                                                                                                                                                                                                                                                                                                                                                                          |                                                                                                                                                                                                                                                                                                                                                                                                                                                                                                          |

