## 7. TRIAL DESIGN

SCALE is a cluster-randomised trial of TB/HIV active case-finding with constrained randomization (1:1 ratio) of 72 clusters of ~4,400 adults per cluster, with boundaries defined by community health worker catchment areas

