## 14. STATISTICS

### 14.1. Sample size justification

Sample sizes were initially calculated assuming a decline from the last National TB Prevalence Survey in 2013-14 given that there has been case-finding activity since then. However, the interim results from a **pre-intervention survey** show greater than anticipated decline (target of 14,511 participants will give precision of +/- 2.5 around an assumed true prevalence of 900 per 100,000 adults, assuming design effect of 1.5 from random household sampling. The increase to 15,500 allows for wastage from e.g. unreadable Xray/contaminated cultures).

Sample size calculations and statistical analyses will use established approaches for cluster-randomised trials.

The **primary trial outcome** has been changed from self-reported testing outcome to TB case notification.

For this, we assume an annual case-notification of adult microbiologically-confirmed TB to be in the range of 70 to 100 per 100,000 adults for the standard of care clusters, based on current data and trends.

An adult population of ~150,000 per arm followed over 12 months will then provide power to detect a 44% to 56% increase in microbiologically confirmed TB if  $k = 0.3$  to  $0.4$ .

Analysis will use standard methods appropriate for cluster-randomised trials, with adjustment for pre-intervention rates of adult microbiologically-confirmed TB.

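### TB cases found by the pre-intervention survey can enter the primary outcome in both arms and pull the rate ratio towards 1, by an amount that the stated timing leaves open

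*Combined protocol and SAP*

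**What the plan says.** **Survey.** Section 10.4.1 samples households at random in the clusters of both arms, with a target of 215 adults per cluster. Survey Xpert and microscopy results are due within 2 days and culture within 6 weeks. On linkage it says: "Patients with positive TB results will have confirmatory specimens taken, while being assisted to register for TB treatment at the nearest TB Registration Centre".

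**Outcome.** Section 9.1 takes the primary outcome from entries in the District electronic TB treatment register and laboratory records, assigned to clusters by GPS residence. Under section 9.3.3 a registering patient is sputum-positive "if they have at least one positive sputum microscopy or Xpert test recorded, regardless of source (routine, or research laboratory"). A patient with culture evidence only must have *M. tuberculosis* grown from the registration specimen. No section excludes, flags or separately analyses registrations that began with the survey.

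**Timing.** Section 3.7 has the trial "with the ACF Intervention and all surveys delivered during June 2019 to March 2020". The synopsis gives the recruitment period as "June 2019-Mar 2020: pre-intervention survey and ACF Round 1", with cluster starts staggered over 9 months. Section 5.1.1 describes the survey as the study's first phase. The outcome window opens at the first ACF visit. It lasts 3 months in sections 3.5, 7 and 9.1 and in the synopsis, but 12 months in the outcomes table of section 9.1 and in the sample size of section 14.1. The survey-to-ACF interval within a cluster is not stated. Nor is the date on which the window opens in a standard-of-care cluster, which has no ACF visit.

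**The concern.** The survey uses X-ray, Xpert and culture to find undiagnosed TB in both arms and sends what it finds to the register from which the trial's events are counted. These registrations come from a research procedure and say nothing about what ACF adds. If about the same number is added to each arm's numerator, the rate ratio moves towards 1 and the extra counts add noise. The expected number of control events in a 3-month window is small, so a modest number of survey cases could matter.

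Cases that register before the window opens are outside the numerator. They may instead enter the pre-intervention notification rate that section 14.1 uses for adjustment, because the period for that covariate is not defined.

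**Working it through.** **Inputs.**
- Section 7: "constrained randomization (1:1 ratio) of 72 clusters of ~4,400 adults per cluster", so 36 clusters per arm.
- Section 10.4.1: 215 survey participants per cluster.
- Section 5.1.1: interim survey yield of 200 per 100,000.
- Section 14.1: about 150,000 adults per arm; control rate "in the range of 70 to 100 per 100,000 adults for the standard of care clusters" per year; k = 0.3 to 0.4.
- Alpha and power are not stated. I assume two-sided 0.05 and 80%.

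**Step 1. Reproduce the plan's own figure.** Section 14.1 says: "An adult population of ~150,000 per arm followed over 12 months will then provide power to detect a 44% to 56% increase". I used the unmatched cluster-trial formula for rates,

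c = 1 + (z_α/2 + z_β)² × [(λ0 + λ1)/y + k²(λ0² + λ1²)] / (λ0 − λ1)²,

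with c = 36 and y = 150,000/36 = 4,167 person-years per cluster. It gives a detectable increase of 44.0% (rate 100, k = 0.3) and 56.7% (rate 70, k = 0.4; 55.7% without the +1 term). This matches 44% to 56%, so the inputs are read as the plan intends. Assuming 90% power (52.1% to 67.7%) or one-sided 0.05 (38.4% to 49.2%) does not reproduce the range.

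**Step 2. Survey cases per arm.** 36 × 215 = 7,740 adults, and 7,740 × 200/100,000 = 15.5 cases.

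**Step 3. Expected control events per arm (B).**
- 12 months: 150,000 × 70 to 100 per 100,000 = 105 to 150.
- 3 months: one quarter of that, 26.25 to 37.5.

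All survey cases together would equal 15.5/37.5 = 41% to 15.5/26.25 = 59% of the expected control events in 3 months, and 10% to 15% in 12 months.

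**Step 4. Dilution.** With S survey cases registered inside the window in each arm, the observed ratio is (B × RR + S)/(B + S). For example, at rate 70 over 3 months with all inside: (26.25 × 1.56 + 15.48)/(26.25 + 15.48) = 56.43/41.73 = 1.35. Ranges below run from rate 70 to rate 100.

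| Window | Share inside | S per arm | True RR 1.44 | True RR 1.56 |
|---|---|---|---|---|
| Either | none | 0 | 1.44 | 1.56 |
| 3 months | a quarter | 3.9 | 1.38 to 1.40 | 1.49 to 1.51 |
| 3 months | half | 7.7 | 1.34 to 1.37 | 1.43 to 1.46 |
| 3 months | all | 15.5 | 1.28 to 1.31 | 1.35 to 1.40 |
| 12 months | all | 15.5 | 1.38 to 1.40 | 1.49 to 1.51 |

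**Step 5. Rate difference and power.** (B × RR + S) − (B + S) = B(RR − 1), so the difference in events does not change. Its variance does rise. For a true ratio of 1.56 over 3 months at k = 0.3, power from the Step 1 formula falls from 40% to 28% (rate 70) or from 51% to 40% (rate 100) if all survey cases fall inside.

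**The case against.** **Timing.** The survey is pre-intervention by name and by phase. The shared dates in section 3.7 and the synopsis are trial-wide and do not show overlap within any cluster. Xpert and smear positives have results within 2 days and could register well before ACF arrives. Only culture-only positives wait up to 6 weeks, and under section 9.3.3 a survey culture alone does not make a registrant a confirmed case. This stands: the lower end of the range is no dilution. A reader might infer that survey cases are certainly in the primary outcome, and the documents do not support that.

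**Case definition.** Section 9.3.3 is headed for routinely diagnosed patients, and survey cases have their own definition in section 9.3.1. The mention of the research laboratory may simply mean registration sputum processed there. This stands in part. The rule was probably not written to capture survey cases, but its operative words apply to registering patients and do not keep survey cases out.

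**Comparator.** Control is an enhanced standard of care, and the survey runs equally in both arms. Balanced additions do not create a spurious effect and leave the rate difference intact, and the plan never names the ratio as its effect measure. That is right, but section 14.1 states the target as a percentage increase, and precision falls on either scale. Section 7 does not list the survey as part of enhanced standard of care.

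**Differential bias.** Because the standard-of-care window start is undefined, a reader might infer that survey cases could fall mainly in control windows and bias the comparison. Nothing in the documents suggests such a pattern.

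**Future SAP.** Section 14.2 defers detail to a plan still to be written. That is the right place for the remedy, but the counting rule already stands in the protocol.

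**Conclusion.** The point holds as a conditional one. The route from survey to register to primary numerator is documented and nothing blocks it. How many cases take it depends on dates that the protocol does not give. For a true rate ratio of 1.56, the observed ratio lies between 1.56 (none inside) and 1.35 to 1.40 (all inside 3 months), or 1.49 to 1.51 if all fall inside 12 months.

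The all-inside figures are upper bounds on dilution. They assume:
- equal survey yield in the two arms;
- full linkage to treatment;
- every survey case meeting section 9.3.3;
- no survey case that would have been notified, or found by ACF, anyway.

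They also rest on the interim yield of 200 per 100,000. The planning prevalence of 900 per 100,000 in section 14.1 would give about 70 cases per arm (7,740 × 0.009), but the plan's own interim result has superseded it, so it should not be used to size the problem.

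**What to change.** In sections 9.1 and 9.3.3 and in the SAP:

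1. Define the date on which the outcome window opens in each standard-of-care cluster, and record each cluster's survey dates and survey-to-window interval.
2. Flag survey-detected registrations in both arms by matching register entries to the study's own survey referral forms (Appendix 1, item 1.14) or survey laboratory records.
3. Exclude flagged registrations from the primary numerator in both arms where the cluster's survey preceded its window. The condition matters: a survey done after ACF would find cases that ACF had missed, and excluding them would then depend on allocation.
4. Exclude them also from the pre-intervention rate used for adjustment, and state the period of that covariate.
5. Report the all-registrations count as a sensitivity analysis.
6. Reconcile the 3-month and 12-month windows, since the choice sets the size of the effect.

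**Cost.** The work is a record match and a few lines of text. Up to about 15 events per arm leave the numerator, including a few people who would have been notified or found by ACF anyway. Section 10.5.1 says that electronic records hold no names, and interim survey results already exist, so matching may be partly retrospective and incomplete. The match should be made without reference to allocation, and its completeness reported by arm.

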#### **10.4.2. ACF intervention participants**

Clusters will be visited for one to two weeks on 1 occasion by a mobile outreach team.

As previously described (21,24) ACF team members will carry out brief household visits, with door-to-door enquiry for chronic cough and leafleting (Appendix 2.1a&b information sheet). As detailed previously, all households with a symptomatic adult ( $\geq 18$  years) member (including those with symptoms reported by another household member in their absence) will be provided with 2 sputum collection containers for each symptomatic individual, together with information leaflets and informed consent forms, and pictorial instructions on how to produce sputum sample (Appendix 2.1a&b information sheet and consent form and Appendix 2.4 CRF).

The ACF team will visit the household on the following day, in order to collect consent forms for cases of reported cough and specimens, which will be tested using sputum microscopy (Appendix 2.5 CRF).

An oral HIV self-testing kit will also be offered with pre-test information to each ACF participant unless already known to be HIV-positive. Kits will be distributed, and oral consent documented by thumbprint, either at the time of initial identification of chronic cough (if present in person), or through a second visit at a likely more convenient time for individuals who are not present at the time of the initial door-to-door visit. Oral consent will be obtained for HIV self-testing, documented by a thumbprint (Appendix 2.2 a&b oral consent and Appendix 2.3 a&b thumbprint consent form). Names will not be recorded and witnesses will not be used to maximise participation and ensure complete confidentiality in line with the Malawi HIV Prevention and Management Act.

Information on how to use the self-testing kit, and what steps to take will be provided in person, and post-test counselling, confirmatory testing and referral for ART if self-test positive will be managed by the ACF team (Appendix 2.8a&b self-referral form, Appendix 2.9 referral to ACF team for confirmatory testing and Appendix 2.7 referral form).

Newly diagnosed ACF participants who are HIV-positive will be asked to provide a urine sample for point-of-care LF-LAM testing for TB, with results provided immediately.

Results of sputum microscopy will be delivered back to participants at a pre-defined results collection point 2 to 4 working days after collection. Participants with positive smears who do not attend for results collection will be visited at home.

All participants with positive TB results will be assisted or accompanied to attend the nearest TB registration centre for treatment registration (Appendix 2.5 TB referral form).

